#### 4. Type of study

Randomized, open label, multicenter (23 sites), prospective trial comparing the efficacy of two strategies to obtain a clinical remission of the nephrotic syndrome 1 year after diagnosis of iMN with anti-PLA2R1 antibodies. As this project is research with category 1 involvement of human beings, it is subject to the provisions of the French Public Health (Law n°2012-300 of 5 March 2012) regarding research involving human beings, as altered by decree n°2016-800 of 16 June 2016.

The study will last 6 years: inclusion period will last 4 years with 2 years of follow-up.

#### 5. Benefit/ Risk

##### Benefit

- At the individual level:

Our recent works on the identification of nephrotoxic autoantibody activity should contribute to improve the individual management of patients with MN, and help to better select patients who should benefit from early and aggressive immunosuppressive strategies. Patients in the personalized arm should expect a remission rate around 85% at 12 months.

- At the collective level:

If the personalized strategy is validated, we should improve the remission rate and decrease the risk of serious adverse events in iMN treatment. Moreover, ancillary studies will help us to understand resistant forms of iMN and proposed new immune therapy like inducing TReg therapy, or Memory B-cell targeting in recurrent forms.

##### Risk

With a dose of 375 mg/mm^2, the most frequently observed adverse drug reactions (ADRs) in patients receiving rituximab were infusions related reactions (IRRs) which occurred in the majority of patients during the first infusion. The incidence of infusion-related symptoms decreases substantially with subsequent infusions and is less than 1% after eight doses of rituximab.

Infectious events (predominantly bacterial and viral) occurred in approximately 30-55% of patients during clinical trials in patients with NHL and in 30-50% of patients during clinical trials in patients with CLL

The most frequent reported or observed serious adverse drug reactions were:

- IRRs (including cytokine-release syndrome, tumor-lysis syndrome), see page 34
- Infections, see page 34
- Cardiovascular events, see page 34

Other serious ADRs reported include hepatitis B reactivation and multifocal leukoencephalopathy (page 34)

With a dose of 1g/mm^2, the most frequent adverse reactions considered due to receipt of rituximab were IRRs. The overall incidence of IRRs in clinical trials was 23% with the first infusion and decreased with subsequent infusions. Serious IRRs were uncommon (0.5% of patients) and were predominantly seen during the initial course. In addition to adverse reactions seen in RA clinical trials for rituximab, progressive multifocal leukoencephalopathy (PML) (page 34) and serum sickness-like reaction have been reported during post marketing experience.

Our protocol does not increase the number of visits of a conventional follow-up.

Conclusion: All things considered, the risk/benefit balance appears to be favorable in this study.

## **6. Selection and exclusion criteria for study participants**

### **6.1 Inclusion criteria**

- Age 18 years or more
- Anti-PLA2R1 activity detected by ELISA or Euroimmune IFA
- Nephrotic syndrome defined by proteinuria > 3.5 g/24h (or UPCR > 3.5 g/g) and serum albumin < 30 g/L at diagnosis
- eGFR (CKD-EPI) > 30 ml/min/1.73 m^2 at diagnosis
- Symptomatic treatment according to KDIGO guidelines: maximal tolerated dose of NIAT (angiotensin-converting enzyme inhibitor and/or angiotensin 2 receptor blockers, diuretics and statins)
- Medical insurance
- Signed informed consent
- Having understood and accepted the need for long-term medical follow-up
- Woman of child-bearing age must be using an effective method of contraception

## 6.2 Exclusion criteria

- Secondary MN: MN related to cancer, infectious, systemic lupus erythematosus, drug
- Anti-PLA2R1 antibodies not confirmed by central analysis (in this case the patient will be replaced)
- Pregnancy or breastfeeding
- Immunosuppressive treatment in the 6 last months
- Presence of anti-rituximab antibodies for relapsed patients
- Cancer under treatment
- Patient with complicated nephrotic syndrome that would require early immunosuppressive treatment (thrombosis, acute renal failure...)
- Patients with active, severe infections or active hepatitis B
- Hypersensitivity to the active substance or to murine proteins, or to any of the other excipients
- Patients in a severely immunocompromised state
- Severe heart failure (New York Heart Association Class IV) or severe, uncontrolled cardiac disease
- Patients unable to give an informed consent

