| Description of the conduct study                                                                                                                                                                                                                                                                                                                                                                                                                                                                                                                                                                                                                                                                                                                                                                                                                                                                                                                                    |
| 
Patients with clinical diagnosis of MN will be tested for the presence of PLA2R1-Ab according to local practices. The selection of the patients fulfilling the inclusion criteria will not delay the start of the symptomatic treatment according to KDIGO guidelines. If the patient meets the criteria for enrollment in the study, they will be informed of the study by the referring nephrologist. Full information will be supplied orally, together with written information. After signing informed consent, blood samples will be shipped to Nice University hospital to analyze the anti-PLA2R1 epitope profiles and anti-rituximab antibodies. Once confirmation of inclusion criteria, patients will be randomized 1/1 between conventional and personalized treatments. All patients will be re-evaluated post-treatment (symptomatic or rituximab) at M3, M6, M9, M12, M18 and M24, with centrally analyzed anti-PLA2R1 activity and epitope profile.
 |

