### **8.2 Patient selection for this study**

Patients with clinical diagnosis of MN will be tested for the presence of PLA2R1-Ab according to local practices. The selection of the patients fulfilling the inclusion criteria will not delay the start of the symptomatic treatment according to KDIGO guidelines. If the patient meets the criteria for recruitment to the study, they will be informed of the study by the referring nephrologist. Full information will be supplied orally, together with written information.

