### **8.3 Inclusion and randomization = M0**

After signing the study consent, participants will be randomized in one of the two treatment arms:

- GEMRITUX treatment
- Personalized treatment

Randomization will be balanced (1:1). Centralized block randomization will be conducted by the *Département de la Recherche Clinique et de l'Innovation* (DRCI) (Department of Clinical Research and Innovation) at CHU Nice (Nice University Hospital). Taking into account the size of our study

sample which is relatively small and the high number of participating centers, (which is high in light of the need to ensure that the intended level of recruitment is met), it does not seem appropriate to account for the center as a stratification parameter.

Randomization will be integrated in the electronic case report file (e-CRF) devised specifically for the study with Redcap® software. Using their personal access details to login, the investigator will provide the necessary patient information (i.e. the first letter of their first and last name and their month and year of birth) for random allocation to treatment by the online randomization module (Redcap®). Randomization can then take place around the clock. The treatment group and inclusion number for the patient will then be relayed to the investigator and the central lab team. The patient's trial records will then be created automatically, allowing data to be entered.

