### **8.7 Specimen collection:**

Non-fasted blood samples will be shipped on the same day at room temperature to the Laboratory of Immunology in Nice, overseen by [name] (see instructions in manual lab), except for the tubes of lithium heparin (collected at inclusion and at first remission) that must be immediately stored at 4°C and shipped at 4°C. They will be analyzed and results will be provided to the study site within 48 hours. All samples will be retained after analysis (except if consent for this is withdrawn) to pursue other research goals (they will constitute a collection) and will be stored at -80°C in a secured fridge/freezer located in the Laboratory of Immunology in Nice Hospital. No genetic study

will be performed on the samples. The Nice University Hospital where the collection is stored will be responsible for declaring it to the Research minister and the Agence Régionale d'Hospitalisation. The cell bank has all of the necessary informatic tools and software necessary for conformance with the national bioethical legislation (loi de Bioéthique). The rules governing sample anonymity will be followed.

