## **12. Statistical analysis**

### **12.1 Analysis strategy**

The statistical analyses will be performed by the biostatistician of the Delegation of Clinical Research and Innovation (DRCI) at the Nice center.

Before each analysis is performed, the conditions for the application of the tests that were used will be verified. The various tests will be considered significant at a threshold of 5% (unless otherwise specified). Continuous variables will be described using the number of observations (N), arithmetic mean (Mean), standard deviation, minimum (MIN), median (Median), and maximum (MAX) values. Categorical variables will be summarized by absolute (N) and relative frequencies (%). The statistical analysis will be performed using SAS Enterprise Guide 5.1 software (Copyright (c) 2012 by SAS Institute Inc., Cary, NC, USA). The statistical analysis will be performed using SAS Enterprise Guide 5.1 software (Copyright (c) 2012 by SAS Institute Inc., Cary, NC, USA).

Population analyzed:

The study patients will be analyzed according to the intention to treat principle (ITT). Each patient will be analyzed as a part of the group to which he or she was assigned at randomization.

A *per protocol* analysis will also be performed, though the results of this analysis cannot be substituted for those of the intention to treat analysis.

Missing data:

The “last observation carried forward” (LOCF) strategy will be used to impute the missing data for the principal objective and, when possible, for the secondary objectives.

Disposition of patients:

According to the CONSORT 2010 statements, a flow diagram of the progress through the phases (enrollment, allocation, follow-up, and analysis) of this study will be presented. The number of screening failures and reasons for screening failures will be summarized. The characteristics of patients lost to follow-up over the course of the study will be reported.

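### The synopsis confirms eligibility centrally before randomization, but Section 8 randomizes first, so two exclusion criteria can remove patients who already have an arm

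*Protocol*

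**What the plan says.** Entry rests on a local antibody test. Section 6.1 asks for "Anti-PLA2R1 activity detected by ELISA or Euroimmune IFA", and Section 8.2 leaves the test to the sites: "Patients with clinical diagnosis of MN will be tested for the presence of PLA2R1-Ab according to local practices". Section 6.2 then adds two exclusions that need the central laboratory. One is "Anti-PLA2R1 antibodies not confirmed by central analysis (in this case the patient will be replaced". The other is the presence of anti-rituximab antibodies in relapsed patients.

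On timing, the synopsis has blood shipped to Nice after consent, and then: "Once confirmation of inclusion criteria, patients will be randomized 1/1 between conventional and personalized treatments". Section 8.3 has a different sequence: "After signing the study consent, participants will be randomized in one of the two treatment arms". It continues: "The treatment group and inclusion number for the patient will then be relayed to the investigator and the central lab team". Section 8.5 has the central tubes shipped at the combined inclusion and randomization visit, and Section 8.7 says of the samples: "They will be analyzed and results will be provided to the study site within 48 hours".

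For the analysis, Section 12.1 applies intention to treat: "Each patient will be analyzed as a part of the group to which he or she was assigned at randomization".

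**The concern.** If randomization comes first, an eligibility test becomes a post-randomization exclusion. Excluding randomized patients on a sample taken before treatment can be harmless when the result is read and acted on without knowledge of the arm. Section 8.3 gives up that safeguard by passing the arm to the laboratory whose result triggers the exclusion, in a trial that is open label for everyone else.

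Replacement adds a second difficulty. If the replaced patient leaves the analysis, the groups compared are no longer those formed by randomization. If that patient stays, the primary analysis includes patients without centrally confirmed disease, for whom the sample size makes no provision.

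**Working it through.** **1. The order of steps, side by side.**

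| Source in the protocol | Order given |
|---|---|
| Synopsis, conduct of the study | consent, central sample shipped, criteria confirmed, randomization |
| Section 8.3 | consent, randomization, arm sent to investigator and central laboratory |
| Section 8.4 | rituximab planned 5 to 14 days after randomization, depending on an epitope result then still awaited |
| Section 8.5, M0 | central tubes shipped at the inclusion/randomization visit; next visit in the personalized arm planned from a result due within 48 hours |
| Schedule of assessments | selection criteria, consent, randomization, PLA2R1 antibodies, epitope profile and anti-rituximab antibodies all in the M0 column; no screening column |

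Sections 8.3 to 8.5 and the schedule agree with one another and disagree with the synopsis. Nothing in Section 8 makes randomization wait for the central result.

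**2. Criteria that depend on the pending sample.** There are two: central confirmation of anti-PLA2R1 antibodies, and absence of anti-rituximab antibodies in relapsed patients. Both are measured on the M0 blood.

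**3. The plan's own sample size.** Inputs from Section 7: 45% and 80% remission, 1:1 allocation, 29 per group, 10% loss to follow-up, 64 in total. The uncorrected two-sided chi-square formula at 5% with 80% power gives

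n = [1.960 × √(2 × 0.625 × 0.375) + 0.842 × √(0.45 × 0.55 + 0.80 × 0.20)]² / 0.35² = (1.342 + 0.537)² / 0.1225 = 28.8, so 29 per group.

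The total is 58 × 1.10 = 63.8, so 64. Both figures reproduce. (Section 7.2 prints alpha as 0.20 and beta as 0.05, which appear to be swapped. That is a separate point.) The only allowance is for loss to follow-up.

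**4. Size, over an assumed range q of central non-confirmation.** The documents give no rate. The expected number among 64 is 64 × q, and the number to randomize for 64 confirmed patients is 64 / (1 − q). If unconfirmed patients stay in the analysis and remit at the same rate in both arms (assumed 30% to 80%), the expected difference shrinks from 0.35 to 0.35 × (1 − q). Chi-square power at 29 per arm, 0.80 with no dilution, then becomes:

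| q (assumed) | Unconfirmed of 64 | Randomized for 64 confirmed | Power at 29 per arm | n per arm for 80% power |
|---|---|---|---|---|
| 2% | 1.3 | 66 | 0.78–0.79 | 30–31 |
| 5% | 3.2 | 68 | 0.75–0.76 | 32–33 |
| 10% | 6.4 | 72 | 0.69–0.72 | 36–37 |

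If confirmation precedes randomization, q is zero among randomized patients, and 29 per group and 64 in total are unaffected.

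**The case against.** The strongest reply is that only the order of steps is in conflict and that everything else is inference. Much of this stands.

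- No section says that a replaced patient leaves the analysis. Replacement may mean only that one more patient is recruited, and the detailed definition of analysis sets may sit in a statistical analysis plan that is not shown. A reader might infer that the intention-to-treat principle is broken outright. The text supports less: the two rules conflict unless the replaced patient is kept.
- A reader might infer that the central laboratory decides the exclusion. The protocol says only that its result triggers it, and names no one as deciding. The test is an assay on blood taken before rituximab in both arms, and nothing shows that a reading would depend on the arm.
- Local positivity is already required, so discordance may be rare.
- The laboratory could not stay blind for long in any case, because it measures rituximab levels in both arms from M3. This limits the request on masking to the eligibility result.
- Since Section 8.7 returns results without distinction by arm, a reader might infer that control sites will withdraw or treat early the patients with epitope spreading. The documents do not establish this. Section 8.5 ties the epitope result to planning in the personalized arm only, Section 9.3 prohibits immunosuppressive agents during the study, and no withdrawal rate is given. Withholding results from control physicians would be an information policy with ethical consequences, and it is not proposed here.

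What the reply does not remove is the contradiction itself. A site working from Section 8 will randomize first, and Section 6.2 then applies to someone who already has an arm.

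**Conclusion.** The point holds as an internal contradiction with a real consequence. The synopsis and Section 8 give different orders. Under Section 8, two exclusion criteria act after randomization, on results from a laboratory that has been told the arm. Replacement then cannot be squared with Section 12.1 unless the replaced patient remains in the analysis.

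The size is unknown. On an assumed 2% to 10%, about 1 to 6 of 64 patients are affected. Keeping them in the analysis without extra recruitment lowers chi-square power at 29 per arm from 0.80 to between 0.69 and 0.79. That assumes unconfirmed patients remit equally often in both arms.

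Two stronger conclusions are tempting and not supported. One is that the primary result would hinge on a single excluded patient. The planned rates correspond to about 13/29 against 23/29, with a chi-square p of about 0.007. Even if three responders were lost from the personalized arm alone (13/29 against 20/26), p would be 0.015. The other is that replacement destroys the block randomization. A few extra allocations may leave the arms slightly unequal in number, but that is not bias, and the protocol gives neither the block size nor a replacement procedure.

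**What to change.** Amend Sections 8.3 to 8.5 and the schedule of assessments to the synopsis order: consent; central sample; central confirmation of anti-PLA2R1 antibodies and, in relapsed patients, of the absence of anti-rituximab antibodies; then randomization in REDCap. Patients who fail either test become screen failures. State in Section 6.2 and in the synopsis list that replacement means only that recruitment continues.

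In Section 8.3, do not relay the arm to the central laboratory before the eligibility result is recorded. In Section 12.1, add that any patient randomized before confirmation stays in the intention-to-treat set in the assigned group.

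The cost is protocol wording, a check in REDCap that blocks randomization until the central result is entered, and a delay of shipping time plus about 48 hours. Since randomization is online at any hour, the patient need not be on site for it. The schedule should state that the baseline sample precedes randomization by a few days. Treatment and visit windows counted from randomization can stay as written, and the sample size does not change.

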## 7. Sample size calculation

### 7.1 Estimate of remission rate in the personalized arm

According to our preliminary data, about 30% of patient with iMN have CysR restricted activity at diagnosis. About 50% will enter in spontaneous remission after 6 months of NIAT and 40% after NIAT + Rituximab at low doses (375 mg/m^2 D0 and D7).

About 70% of patients have CTLD1/7 activity, in our cohorts, about 85% entered in remission after repeated pulses of high doses of rituximab.

We therefore expect a remission rate of 80% at M12 in the personalized arm.

### 7.2 Estimate of remission rate in the control arm

Based on data from the literature 10-21% of iMN patient with nephrotic syndrome entered into spontaneous remission after 1-year of NIAT (11, 18) and 35% in GEMRITUX after NIAT + low doses of rituximab (375 mg/m^2 D0 and D7) (18).

We expect a remission rate of 45% in the control arm.

With  $\alpha=0,20$  and  $\beta=0.05$  (two-sided test), the number of patients required is 29 in each group (Nquery© Advisor v 7.0, two group Fisher's-exact test). To account for a 10% rate of lost to follow-up (anticipated as minor in this study as patients are intensively followed for this pathology), the global sample size is 64 patients.

This sample size is large in the frame of this study because the medical condition studied here is rare. Actually, we can expect an annual eligible number of patients of 1 or 2 in the 23 centers, which are in charge of almost all the cases nationally (reference centers). Since 50% of patients may refuse to participate, we estimate that 4 years are required to recruit the calculated sample size.

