## **12.3 Outcomes analyses**

### **12.3.1 Analysis of the primary objective:**

The primary objective of this study is to compare the clinical remission rate over one year between patients with and without personalized treatment.

The clinical remission rate at M12 will be compared between the groups using a Chi-square test or Fisher's exact test in case of small sample.

If necessary, a multivariate logistic regression analysis will be performed to assess the relationship between the clinical remission and the treatment group, adjusted for the potential confounding factors.

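### The sample size section prints alpha 0.20 and beta 0.05 against a 5% analysis threshold, and credits 29 per arm to a Fisher exact test that has 71% power there; the figure matches an uncorrected chi-square test

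*Protocol*

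**What the plan says.** Section 7.1 sets the planning rate for the personalized arm: "We therefore expect a remission rate of 80% at M12 in the personalized arm". Section 7.2 sets the control rate: "We expect a remission rate of 45% in the control arm".

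Section 7.2 then prints alpha as 0.20 and beta as 0.05, continues "two-sided test), the number of patients required is 29 in each group", and gives the method as a "two group Fisher's-exact test". An allowance of 10% for loss to follow-up brings the total to 64. Allocation is 1:1 (Section 8.3).

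Section 12.1 says: "The various tests will be considered significant at a threshold of 5% (unless otherwise specified". It also prescribes intention-to-treat analysis, with last observation carried forward for missing primary data.

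Section 12.3.1 compares the month-12 remission rates "using a Chi-square test or Fisher's exact test in case of small sample". It does not say what counts as small.

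Section 5, under Benefit, gives another expected rate: "Patients in the personalized arm should expect a remission rate around 85% at 12 months".

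**The concern.** The error rates, the power and the test behind the sample size should agree with each other and with the analysis. Here they do not, in three respects.

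- **Error rates.** Read as printed, Section 7.2 plans for a 20% two-sided type I error and 95% power. Section 12.1 tests at 5% unless something else is specified, and a reader could take Section 7.2 to be that specification. The primary significance level of a confirmatory trial should not be open to that reading.
- **Planning test.** The number is credited to Fisher's exact test. That test is conservative in samples of this size and needs more patients than the chi-square formula.
- **Analysis test.** Section 12.3.1 makes chi-square the default, which is not the test named for planning.

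At stake is whether the power that the trial reports belongs to the test that it will run.

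**Working it through.** **Inputs.** p1 = 0.45 (Section 7.2), p2 = 0.80 (Section 7.1), 1:1 allocation (Section 8.3), two-sided test (Section 7.2). Error rates: as printed (alpha 0.20, beta 0.05) and exchanged (alpha 0.05, beta 0.20).

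Mean rate = 0.625. Difference squared = 0.35² = 0.1225. p1(1 − p1) + p2(1 − p2) = 0.2475 + 0.16 = 0.4075.

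**Step 1: reproduce 29 per arm.** The uncorrected chi-square formula with pooled variance under the null hypothesis is

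n = [z(1 − α/2)·√(2 × 0.625 × 0.375) + z(1 − β)·√0.4075]² / 0.1225

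- alpha 0.05, power 80%: (1.960 × 0.6847 + 0.842 × 0.6384)² / 0.1225 = 28.8, so **29**.
- alpha 0.20, power 95%: (1.282 × 0.6847 + 1.645 × 0.6384)² / 0.1225 = 30.3, so 31.

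The unpooled formula, n = [z(1 − α/2) + z(1 − β)]² × 0.4075 / 0.1225, gives:

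- alpha 0.20, power 95%: 28.5, so 29.
- alpha 0.05, power 80%: 26.1, so 27.

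**Step 2: exact power of the named test.** All outcome pairs (x, y) were enumerated with their binomial probabilities. The two-sided Fisher p-value and the uncorrected chi-square p-value were computed for each pair, and the probabilities of the significant pairs were summed.

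| Per arm | Fisher, alpha 0.05 | Chi-square, alpha 0.05 | Fisher, alpha 0.20 |
|---|---|---|---|
| 29 | 71.3% | 79.6% | 91.1% |
| 32 | 78.3% | 85.2% | 93.0% |
| 33 | 80.0% | 86.8% | 92.9% |
| 36 | 82.4% | 88.8% | 94.5% |
| 37 | 83.9% | 88.9% | 95.2% |

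A two-sided Fisher test therefore needs 33 per arm for 80% power at 5%, and 37 per arm for 95% power at 20%. Neither reading gives 29.

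**Step 3: which test would Section 12.3.1 select at the planned rates?** With 29 per arm, expected remissions are 0.45 × 29 + 0.80 × 29 = 36.25 of 58. The expected counts per arm are then 18.1 remissions and 10.9 non-remissions. The smallest is about 11, so a conventional expected-count rule would select chi-square.

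**Step 4: does chi-square hold its level?** At 29 per arm its exact type I error is 4.6% to 4.8% for common remission rates of 0.30 to 0.80, and 5.3% at 0.90. Fisher's is 2.1% to 2.5% for 0.30 to 0.80.

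**Step 5: does the choice of test matter?** At the planned rates and 29 per arm, the probability that chi-square is significant and Fisher is not is 79.6% − 71.3% = 8.3%. For example, 13/29 versus 21/29 gives p = 0.033 by chi-square and p = 0.061 by Fisher.

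**Step 6: 80% or 85%?** With 85% in the personalized arm, Fisher power at 29 per arm rises to 86.0%. Planning on 80% is the more cautious choice.

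**The case against.** Several stronger readings are tempting, and the document does not support them.

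*The printed values cannot give 29.* They can: the unpooled formula with alpha 0.20 and beta 0.05 gives 28.5, and the exact power of chi-square at alpha 0.20 and 29 per arm is 94.8%. A swap is therefore the likely explanation and not a proven one. What is documented is the conflict with the 5% threshold. The unpooled route does not rescue the text either, because it is not the named test and would imply a 20% significance level.

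*The trial is underpowered.* A reader might infer this from 71.3%. That figure holds only if Fisher is the test and 29 per arm are analysed. Intention-to-treat analysis with imputation could bring all 64 patients into the analysis. At 32 per arm Fisher has 78.3% power, still just short of 80%, and chi-square has 85.2%.

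*The primary test is left open.* Section 12.3.1 is a conditional rule with chi-square as the default, and the trigger for Fisher could properly be defined in a statistical analysis plan. An ordinary expected-count reading selects chi-square at the planned rates. It does so in the 13/29 versus 21/29 example too, where the smallest expected count is 12. The divergent p-values matter only if small sample is read unusually. What stands is that planning and analysis name different tests.

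*The planning rates undermine the size.* The 85% in Section 5 is an approximate figure in a benefit statement, and using it would raise power. Section 7.1 gives 40% for remission after low-dose rituximab in CysR-restricted patients, and Section 1.3 gives about 70%. The denominators may differ, so no contradiction is shown.

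**Conclusion.** The point holds as a fault in what Section 7.2 states. The printed alpha of 0.20 contradicts the 5% threshold of Section 12.1. The 29 per arm is credited to a test that does not give it under either reading of the error rates. At 5%, Fisher has 71.3% power at 29 per arm and 78.3% at 32, a shortfall of 8.7 and 1.7 percentage points from 80%. Uncorrected chi-square has 79.6% and 85.2%, so the planned size is adequate for the default test of Section 12.3.1.

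This rests on the planning rates of 45% and 80%, a two-sided test, equal arms, and 80% as the intended power. The last is an inference from the likely swap. The text does not show that the trial will be tested at 20%, or that it is too small for the analysis it is most likely to use. The difference between 80% and 85% is minor.

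**What to change.** 1. **Section 7.2:** restate the calculation as two-sided alpha 0.05, beta 0.20 (power 80%), uncorrected Pearson chi-square test, 45% versus 80%, 29 per arm. Remove the reference to Fisher's exact test.
2. **Section 12.3.1:** name the uncorrected Pearson chi-square test as the single primary test, and delete the Fisher alternative. With a smallest expected count of about 11, it is not needed.
3. **If Fisher is preferred:** name it in both sections and state its power as 71% at 29 per arm, or 78% if all 64 are analysed. Reaching 80% would take 33 per arm before loss.
4. **Section 5:** align the expected personalized-arm rate with the 80% used for planning.

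The cost of items 1, 2 and 4 is a text amendment, best made before outcome data are seen. They leave the 29 per arm unchanged. The loss allowance is a separate rounding matter: 58 × 1.10 = 63.8 gives the stated 64, whereas 58 / 0.90 = 64.4 would give 65. Keeping Fisher costs a less favourable power statement or, at 33 per arm with 10% loss (33 / 0.90 = 36.7, so 37), 74 patients in place of 64.
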